**Fig. 1 Fig1:**
[figure not shown]
Expected flow of participants from recruitment through to the end of the study

We have developed a multiple gating procedure for recruitment. Decisions about eligibility for the trial will be made at three key points: (1) by the referring agencies (i.e. individual Offender Managers across each site) following a discussion with the Specialist Offender Manager (SOM) in the MBT team to identify ostensibly suitable potential participants; (2) through an explanatory meeting between the offender, the MBT team, and the research team following the initial referral, to explain the research trial, invite participation, and answer any questions about the clinical services potentially available to the participant; (3) as a result of discussions between the MBT clinicians, Assistant Psychologist, and Research Manager following an in-depth clinical assessment and formal diagnostic evaluation, to screen out offenders who do not meet the eligibility criteria.

Experience suggests that each of these screens tends to reveal different criteria for ineligibility, and their use in combination minimizes the (considerable) effort of recruitment. For example, the SOM tends to identify and screen out cases whose offending history includes child sex offences, whereas discussions between the MBT and research teams and the potential participant most commonly identify and screen out individuals who are insufficiently motivated to engage with group treatment. The clinical assessment reveals offenders who are ineligible due to their lack of suitability for tolerating a group setting or psychotherapeutic treatment in general, and the formal diagnostic evaluation is necessary to confirm the individual’s psychiatric diagnosis.

#### Screen 1

The SOMs in the MBT teams will work across each of the 13 sites, taking referrals from Offender Managers who will put forward individuals they deem agreeable to being approached about participation and who have adequate English and cognitive capacities to participate in informed consent and group therapy. SOMs will be available to discuss cases that potentially meet the eligibility criteria for MBT. In addition, the SOM and Assistant Psychologist at each site can directly screen for suitable cases by reviewing their caseload against the inclusion and exclusion criteria, before approaching the respective Offender Manager to make a referral.

The decisions made by the SOM constitute the first screen. A standard referral form for each locality is used in liaison with the research team, including specific information pertaining to inclusion and exclusion criteria.

#### Screen 2

Following acceptance of the referral by the MBT team, a meeting will be arranged between the MBT and research teams and the offender, to inform the offender about the trial and the opportunity to participate. The discussions at this meeting include what the MBT intervention would entail and the alternative PAU path (the best available alternative treatment at that locality; see below) should the offender not be randomized to receive MBT. Offenders will be provided with participant information sheets that have been co-designed with input from ex-offenders to make them as useful and accessible as possible. Offenders will be given a minimum of 24 h to consider participation.

#### Screen 3

If the offender decides to participate following the explanatory meeting, an in-depth clinical assessment and formal diagnostic evaluation will be arranged. MBT clinicians will conduct history-taking, administering the SCID-II psychosis screen, and ascertaining the offender’s ability to engage in psychotherapeutic treatment and tolerate a group setting.

Consent forms will be signed by both the offender and the site’s lead MBT clinician, who will assess the offender’s capacity to provide informed consent. Consenting to the trial includes providing permission to access police records, remaining in effect for 2 years, and health records, remaining in effect for 5 years.

The site’s Assistant Psychologist will administer the SCID-II screen and the OAS-M. If all of the inclusion criteria and none of the exclusion criteria are met, the participant will progress to the next stage of the research process to complete the baseline measures.

#### Baseline measures

For offenders who sign the consent forms, the researcher will administer pre-randomization questionnaires and measures to be completed during this contact (i.e. before group assignment). When all the instruments have been completed and eligibility for the trial has been confirmed, randomization will be performed and details communicated to the referrer, MBT team, and participant within 48 h.

#### Randomization and procedures to minimize bias

Following consent and baseline measures, a trial identification number will be assigned to eligible consenting participants and a recruitment ‘dam’ created behind which a participant pool will be built up, from which participants will be randomized to enable MBT groups to start. Once groups have started, sequential assignment will allocate participants to MBT or PAU in a 1:1 ratio. Randomization will be undertaken off-site, using a dynamic adaptive allocation algorithm [76] accessed by a secure web portal to the system held at NWORTH Clinical Trials Unit (CTU) and maintained by a statistician independent of the analysis and research teams to ensure blinding. Stratification will be by site, age (21–25; 26–39; 40+ years), probation order type (Community Sentence; On Licence Post-Prison), and time remaining on probation (less than 12 months; 12 months and over). Treatment site is included in the minimization stratification to control for differences between sites. To minimize bias that could arise from knowledge of treatment allocation, researchers will be blind to participants’ treatment. The allocation to treatment arms will not be modified unless the local principal investigator, with the agreement of the clinical supervisor or the Trial Steering Committee (TSC), identifies severe risks of adverse events (homicide, suicide, serious injury, etc.) associated with the experimental treatment. Experimental treatment will be discontinued if the participant breaks the conditions of probation and is recalled to serve the remainder of their prison sentence for a time which prevents any further attendance or if the participant commits further offences and receives a custodial sentence for the fresh conviction that is longer than the remaining time of treatment.

### Planned interventions

Implementing standard PAU or PAU supplemented with MBT will not require alteration to usual pathways (including use of any medication), and these will continue for both trial arms.

#### PAU

Participants randomized to receive PAU will remain under the supervision of the NPS for the duration of their licence or community sentence. PAU is a well-specified and stringently monitored standard procedure used in the management of offenders under community supervision. It consists of regular contact with a designated Offender Manager for the duration of the offender’s licence or sentence, and includes referral for additional interventions as indicated in Ministry of Justice guidance. PAU participants will be free to be referred by their Offender Manager for any locally available treatment (except MBT) designed to reduce reoffending (e.g. anger management programmes, substance misuse interventions). Provision of these interventions is not uniform across the UK but dependent on local availability; in some areas, there may be no targeted interventions available. Unlike MBT, none of the interventions that participants may receive under PAU involve targeting the capacity to envision mental states more accurately. Details of services accessed under PAU will be documented by the SOM to facilitate economic data collection and evaluation. Additional site-specific strategies (e.g. separate supervision groups) will ensure that MBT principles and practice do not directly influence the management of participants randomized to PAU. PAU will last for 12 months, after which participants who still have time remaining on their licence or community sentence will remain under the supervision of the NPS for the duration. Participants whose licence expires during the trial period may remain under the NPS on a voluntary basis to complete the 12-month period.

#### PAU supplemented with MBT-ASPD

The treatment intervention is a 1-year programme of group and individual sessions of MBT-ASPD. Participants randomized to MBT-ASPD receive weekly group therapy for 75 min and monthly individual therapy for 50 min. Each MBT-ASPD group is run by two trained MBT clinicians and contains a maximum of eight participants, using an ‘open’ rolling entry group, with new participants joining as others leave. The group process enables participants to challenge each other about their understanding of current self-identified critical interpersonal experiences and focuses particularly on elaborating the mental state background of interactions characterized by conflict that might normally trigger aggression. The content of the group therapy sessions is steered by the clinicians toward encouraging the participants to talk about their mental states related to recent violent incidents by linking their actions to a broader range of their current subjective and emotional experience (i.e. to ‘mentalize’ them). A monthly 50-min individual session provides an opportunity for participants to address personal issues that have occurred in the group. Many participants find it more difficult to talk in front of other members of the group about the relationship difficulties they experience in their external lives, and may use the individual sessions to do this too. Both group and individual sessions focus on identifying thoughts and feelings associated with aggressive impulses, with particular emphasis on understanding emotional cues, recognizing emotions in oneself and others, understanding others’ experiences in relation to one’s own, and clarifying threats of loss to mentalizing in the context of life experiences, both currently and historically.

All participants randomized to this arm of the study have an allocated clinician. Staff providing MBT sessions are chartered health professionals with a core clinical training background (e.g. clinical psychology, nursing, medicine) who have undergone an MBT training course. Where possible, recently trained clinicians are paired with an experienced clinician to provide group MBT.

The evaluation of the adequacy of protocol delivery and adherence to the model will include treatment integrity measures based on the MBT Adherence and Competence Scale [77], applied to video recordings of a random sample of sessions. This instrument enables coders to rate therapist activity and appropriateness in five key domains of MBT with ratings on Likert scales supported with anchored descriptors. As clinicians will be specially trained for the trial, it is critical to separately evaluate both clinician adherence and level of clinician competence, which will be based on the independent rating of randomly selected session recordings. The scale measures both the frequency of therapists’ actions (adherence) and the quality of the delivery of those actions (competence). Adherence refers to the number of items used within a domain and their frequency of use; quality refers to the clinician’s demonstration of how the interventions are delivered in terms of (a) expertise, competence, and commitment; (b) timing; (c) taking account of the context and content of the session; (d) matching the mentalizing state of the patient; (e) responding to where the patient appears to be; and (f) an extensiveness component in terms of items used when working in the domain. A definition of skill/quality is given for each domain.

Clinicians with average scores above 3.5 will be considered to have achieved acceptable levels of adherence and competence. Adherence will be monitored on a monthly basis through clinical supervision sessions using the MBT Adherence and Competence Scale, based on independent rating of randomly selected session video recordings, to ensure that clinical staff are consistently on-model.

### Assessments and outcome measures

To maximize the validity of the outcome evaluations, assessments will be made across multiple domains using multiple methods and sources.

#### Primary outcome

The primary outcome is the frequency of aggressive antisocial behaviour as measured by an adapted version of the OAS-M and is collected every 3 months. The OAS-M provides information to establish frequencies of verbal aggression and physical aggression against objects, against others, and against the self. The OAS-M is a robust semi-structured interview and is the most widely used measure of aggression in trials and clinical studies in this area. It has been used with many different outpatient populations, including those with Cluster B personality disorders. It is one of the only measures of aggression that assesses actual aggressive behaviour, and its format offers several advantages over most available instruments for assessing anger and aggression, including allowing the probing of vague and inconsistent answers [67]. It is therefore well suited to accurate evaluation of aggressive behaviour and of change over time, both as a research instrument and as a complement to many of the current self-report measures. In agreement with the developer of the measure, the OAS-M, adapted for the current study, uses a weighted scale taking the number of reported endorsed items and multiplies them in accordance with the severity of each item. Aggression is the primary outcome in this study as it is the key characteristic of ASPD, the primary driver of interpersonal violence, and a key contributor to health status [78, 79]. The primary endpoint is at 12 months post-randomization. As a secondary outcome, the adapted OAS-M is collected at other time points (3, 6, 9, 15, 18, 21 and 24 months).

#### Secondary outcomes

The domains that the investigators consider key to the intervention are violence, anger, offending behaviour, impulsivity, alcohol and substance misuse, self-harm and suicidality, general health and wellbeing, service satisfaction and engagement outcomes, and remission in ASPD diagnostic status. These secondary outcomes will be assessed by using objective and self-report measures. Estimates of the population at risk resource use data relevant to conducting a comprehensive economic evaluation will be collected alongside these outcomes, as well as data on variables associated with putative mechanisms of change.

#### Objective measures

Objective outcomes of health service use will be collected from record linkage using participants’ NHS numbers at 6-monthly intervals during the intervention and the follow-up period until the 24-month follow-up point.

Objective outcomes of offending behaviour, including withdrawal of licence, arrests, and reconvictions, will be collected from police computer records at 6-monthly intervals, for the 6 months before randomization and during the intervention and follow-up period until the 24-month follow-up point. The number of records of offending behaviour (count data) will be obtained, and 6-month periods free of any offending behaviour will also be recorded (binary data). Data will be obtained from participants’ records on nDelius (the national public sector offender case-management system) and the Police National Computer database; these records detail information on breaches of licence conditions, police contacts, charges, court appearances, criminal orders, arrest rates, and frequency, severity, and type (violent/non-violent) of offending behaviour.

These objective outcomes of health service use and offending behaviour will be available regardless of loss to follow-up; this will allow the use of multiple imputation techniques. If loss to follow-up is considerably different between arms and the primary outcome is significant, we will perform a sensitivity analysis to the impact of missing data not being missing at random, as described by White et al. [80].

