### Sample size and power calculation

The sample size (*N* = 302) has been chosen to have 90% power, at a two-sided 5% significance level, to detect a significant difference between groups when the change in OAS-M score is on average 10 points less in the MBT arm (with a standard deviation of 20) at the primary endpoint 12 months after randomization. Hollander et al. [68] reported the pooled standard deviation of the change in OAS-M score from baseline to 10-week follow-up as being just over 9 for the pharmaceutical intervention assessed in that study. Due to the longer follow-up period of the present trial and the non-pharmaceutical nature of the planned intervention, we have chosen to increase the standard deviation used in our power calculation to 20. To take into account potential clustering by clinician in the MBT arm, we assume the intraclass correlation coefficient to be 0.05. In this case, using established methods to take account of clustering [69], 95 participants per arm will give 90% power. We anticipate attrition and dropout to be 37%, based on several sources including our own preliminary work and several larger data sources (a meta-analysis of attrition rate in offender treatment literature [70], a systematic review of non-completion of treatment for personality disorder [71], and an empirical evaluation of treatment disengagement in offenders with personality disorder [72]). To account for this loss, initial recruitment of 151 participants per arm is anticipated to result in 95 participants remaining per arm after attrition and dropout. Our target sample size is therefore 302 participants, which will give sufficient power to detect a medium effect size of 0.5 change in participants’ OAS-M score.

Demographic and clinical details from those refusing randomization will be retained to explore whether the trial population is representative. To assess treatment acceptability, we will compute the proportion of referred individuals who never attended, the number of sessions attended, and the number who drop out of treatment or request to be referred to other treatments. All participants who do not formally withdraw from the study will be followed up on routine measures of outcome.

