#### Secondary outcomes

For the secondary outcomes, we will use mixed-effects linear regression for continuous outcomes, mixed-effects logistic regression models for binary outcomes, and mixed-effects Poisson models for count data such as number of offences. Missing outcome data due to dropout will be accounted for by the mixed-effects model under a missing-at-random assumption; missing covariates will be accounted for using multiple imputation.

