Aggressive antisocial behaviour has been chosen as the primary outcome for this trial, in light of it being a core feature of ASPD, an indicator of emotional wellbeing, and a frequent cause of grounds for arrest. A range of secondary outcomes have also been chosen in order to evaluate MBT’s possible impact on the wide range of symptomatology and health outcomes experienced by individuals with ASPD, including impulsivity, offending behaviour, alcohol and substance misuse, self-harm and suicidality, and general health and wellbeing. The MOAM trial will also provide accurate information about the services accessed under PAU. A comprehensive cost-effectiveness evaluation will be undertaken to examine both costs offset and costs saved in relation to having received MBT or PAU. Thus, the trial will provide unprecedented data not only on the clinical effectiveness and cost-effectiveness of MBT-ASPD, but also on the clinical effectiveness and cost-effectiveness of the usual services available to this group while on probation. Furthermore, the trial will analyse offender referral information to identify trends, calculate the size of the population likely to benefit from an intervention for ASPD, and make recommendations about treatment groupings and targeting of services.

Information to date suggests that the trial protocol detailed above is acceptable to all the sites and that recruitment, data collection, and training are feasible in all locations. Preliminary data on participant engagement indicate that, of participants randomized to MBT, an average of 55–65% attend group MBT sessions. Preliminary data indicate that one third of participants drop out at some point following randomization, entirely consistent with attrition rates reported in other studies involving treatment for offenders and patients with personality disorders [70–72]. For participants who drop out, the average length of engagement with the trial is 3–6 months; the most common reasons for dropout thus far are lack of motivation (58%), recall to prison (35%) and clinicians’ discretion due to repeated non-attendance of MBT sessions (7%).

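### The missing-not-at-random sensitivity analysis is conditional on unequal loss and a significant primary result, and neither condition shows when departures from missing at random matter

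*Protocol article*

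**What the plan says.** Under Objective measures, after noting that health-service and offending records stay available despite loss to follow-up and so permit multiple imputation, the article says: "If loss to follow-up is considerably different between arms and the primary outcome is significant, we will perform a sensitivity analysis". The analysis concerns data not missing at random. The two conditions are joined by 'and', and the article states no other such analysis of the OAS-M.

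The handling of dropout in the models is given under Statistical analysis, Secondary outcomes: "Missing outcome data due to dropout will be accounted for by the mixed-effects model under a missing-at-random assumption". The primary-outcome paragraph specifies a mixed-effects linear model with baseline OAS-M, sentence length and the stratification factors other than site as fixed effects, and makes no separate statement on missing outcomes.

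On the amount of loss, the sample size section says "We anticipate attrition and dropout to be 37" per cent, and "initial recruitment of 151 participants per arm is anticipated to result in 95 participants remaining per arm after attrition and dropout". It also says "All participants who do not formally withdraw from the study will be followed up on routine measures of outcome". The Discussion reports that about one third have dropped out so far and gives pooled reasons: "the most common reasons for dropout thus far are lack of motivation (58%), recall to prison (35" per cent), with the remaining 7% put down to clinicians' discretion over repeated non-attendance of MBT sessions.

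**The concern.** A sensitivity analysis for data missing not at random asks whether the conclusion would survive if the men without a 12-month score differ from what the model predicts for them. The need for it depends on how many are missing and how far they depart from prediction in each arm. The stated rule looks instead at whether the loss rates differ and at the p-value.

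Equal loss rates do not protect the comparison if the missing men depart from prediction by different amounts in the two arms. Nor does a non-significant result: missing data can hide a real effect as easily as create a false one. Under the rule, a trial with balanced loss, or one with a null primary result, could report its main finding with no test of the MAR assumption.

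The article itself gives reason to doubt MAR. Recall to prison, 35% of reported dropouts, is plausibly related to recent aggression, which is the outcome. Clinician discretion over missed MBT sessions, 7% of dropouts, can arise only in the MBT arm.

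**Working it through.** **Inputs from the sample size section.** The trial "has been chosen to have 90% power, at a two-sided 5% significance level" when "the change in OAS-M score is on average 10 points less in the MBT arm (with a standard deviation of 20"). The intraclass correlation is 0.05, for clustering by clinician in the MBT arm. Loss is 37%, with 151 randomised and 95 remaining per arm. No cluster size is stated.

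**Reproducing the plan's figure.**
- Without clustering: 2 x (20 x (1.960 + 1.282)/10)^2 = 84.06, so 85 per arm.
- With clustering in the MBT arm only and m men per cluster, the design effect is 1 + (m - 1) x 0.05. For m = 6 it is 1.25, and n = (84.06/2) x (1 + 1.25) = 94.6, so 95 per arm. The value m = 6 is my assumption, chosen because it returns the stated 95; m = 5 gives 93 and m = 7 gives 97.
- 95/(1 - 0.37) = 150.8, so 151 per arm and 302 in total.

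The standard error this implies is 20 x sqrt((1 + 1.25)/95) = 3.08 points.

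**Bias of a MAR estimate.** Let f be the share missing and d how many OAS-M points worse the missing men are than MAR predicts. Then

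bias = f_MBT x d_MBT - f_PAU x d_PAU,

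which with equal loss reduces to f x (d_MBT - d_PAU).

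**Equal loss of 37%.** The gap d_MBT - d_PAU is an assumption, shown as a range. A positive gap flatters MBT; a gap of the same size the other way hides a benefit. False-positive rate = Phi(bias/SE - 1.96) + Phi(-bias/SE - 1.96). Power for a true 10-point effect = Phi((10 - bias)/SE - 1.96).

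| Gap (points) | Bias (points) | False-positive rate, no true effect | Power for a true 10-point effect, bias toward the null |
|---|---|---|---|
| 0 | 0 | 5% | 90% |
| 2 | 0.37 x 2 = 0.74 | 6% | 85% |
| 5 | 0.37 x 5 = 1.85 | 9% | 75% |
| 10 | 0.37 x 10 = 3.70 | 22-23% | 53% |

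For the last row, 3.70/3.08 = 1.20.

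**Lower loss.** If only the 58% of dropouts reported as lacking motivation were truly missing, the share would be 0.37 x 0.58 = 0.215. A 10-point gap then gives about 2.1 points of bias. The false-positive rate is about 11% with the SE held at 3.08. It is about 12% if the SE is recalculated for 151 x 0.785 = 118.6 men per arm (2.75 points).

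**Does the first condition pick out the larger bias?** Take loss of 42% and 32%, with the missing men 10 points worse than predicted in both arms. Bias is (0.42 - 0.32) x 10 = 1.0 point. That imbalance might trigger the analysis. Equal loss of 37% with a 10-point gap gives 3.7 points and would not.

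**How often would it trigger by chance?** If true loss is 37% in both arms, the observed difference in loss has standard deviation sqrt(2 x 0.37 x 0.63/151) = 0.0556. A difference of 10 percentage points or more arises about 7% of the time. The 10-point cut is illustrative, since the article sets none.

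**The case against.** The strongest reply is that this is one supporting analysis, and that the rule covers a genuine risk case: a positive result with clearly unequal loss. That stands. A reader might infer that the check is skipped precisely whenever it is needed; the text does not support that, because it does run in this case.

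Other tempting readings also go too far:

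- **That 37% of 12-month OAS-M scores will be missing.** The figure combines attrition and dropout, and some of its named sources concern treatment non-completion or disengagement. The article follows up everyone who does not formally withdraw, so 37% is an upper planning value.
- **That the reasons for loss are shown to differ by arm.** The percentages are pooled. Only the 7% for clinician discretion is necessarily confined to MBT: 0.07 x (1/3) x 302 is about 7 men, or 4.7% of 151. That group alone could not produce a 10-point average gap across all dropouts.
- **That the missing cut-off for a considerable difference is itself a fault.** The article defers detail to an analysis plan agreed before unblinding, where a cut-off could be set.
- **That recalled or discharged men are wrongly abandoned.** The article treats qualifying recall as stopping the experimental treatment and keeps non-withdrawn men in follow-up. The Discussion's wording is a progress report, not a follow-up rule.

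The records do make imputation possible, and the article says so just before the rule. Imputation from records makes MAR more plausible but is still a MAR method, so it does not replace the conditional analysis. An analysis plan not shown may contain an unconditional version. The point concerns a rule that the article itself fixes.

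**Conclusion.** The point holds in limited form. The article makes its only stated check on departures from MAR depend on two joint conditions, and neither identifies when those departures matter. Balanced loss can carry more bias than visibly unequal loss, and a non-significant result may itself be a product of missing data.

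The size is conditional. With gaps of 2 to 10 points and loss at the planning value, bias runs from about 0.7 to 3.7 points, or 7% to 37% of the target difference. At about 21% loss the top of that range falls to about 2.1 points. These figures rest on assumed gaps and on about six men per cluster. They show what the rule could let through. They are not evidence that the trial's result is biased, and the documents do not support that inference. The doubt about MAR comes mainly from recall to prison, whose link to aggression is plausible but not stated in the article. The primary model and the sample size are not in question.

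**What to change.** Delete both conditions. Pre-specify, in the protocol and the analysis plan, a delta (pattern-mixture) analysis of the 12-month OAS-M that is run whatever the loss rates or the p-value. Vary delta in the MBT arm alone, in the PAU arm alone and in both, over a stated range such as 0 to 10 points, and report the tipping point at which the conclusion changes.

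As a supporting analysis under MAR, impute the OAS-M with the linked offending and health records as auxiliary variables.

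The article describes follow-up as still in progress and requires the analysis plan to be agreed before unblinding, so the change can be made in time on that account. It costs wording and a few extra model runs, with no new data items, no further interviews and no change to the 302. The downside is that the conclusion may look less certain.
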